| Randomization  R  A  N  D  O  M  I  Z  E  Daily TDF  Daily Placebo  No treatment for 9 months, then daily TDF  No treatment for 9 months, then daily Placebo  Site B  Site A  Site C |  |
| Enrollment: | Over 24 months |
| Main eligibility criteria: | Healthy, HIV-1 negative MSM who reported anal intercourse in the last 12 months |
| Study procedures/frequency: | Physical examinations, behavioral risk assessments, and laboratory analyses at screening, baseline, months 1, 3 and then every 3 months through 24 months of study. |
| Test product, dose, and mode of administration: | TDF 300 mg po QD. |
| Criteria for Evaluation | Safety  Clinical and laboratory adverse events  Risk behavior change  Adherence to study drug  HIV antiretroviral resistance |
| Statistical Methods | The primary endpoints are to assess the safety and tolerability of TDF as determined by the proportion of participants with grade 3 or 4 abnormalities (clinical adverse events and laboratory toxicities occurring after treatment initiation), the difference in reported risk behavior between the immediate and delayed treatment arms, and overall rates of adherence. Intent-to-treat analysis will be used. |

GLOSSARY OF ABBREVIATIONS AND DEFINITION OF TERMS

| 3TC | lamivudine, Epivir® |
| --- | --- |
| 3TC/AZT | lamivudine/zidovudine, Combivir® |
| ACASI | audio-computer administered interview |
| AE | adverse event |
| AIDS | acquired immunodefienciency syndrome |
| ALT (SGPT) | alanine aminotransferase |
| AST (SGOT) | aspartate aminotransferase |
| ART | antiretroviral therapy |
| BUN | blood urea nitrogen |
| CAB | community advisory board |
| CBC | complete blood count |
| CBO | community based organization |
| CK | creatine kinase |
| CLIA | clinical laboratory improvement amendments |
| CrCl | calculated creatinine clearance |
| CRF | case report form(s) |
| CRO | contract research organization |
| d4T | stavudine, Zerit® |
| DHHS | Department of Health and Human Services |
| ddI | didanosine, Videx® |
| dL | Deciliter |
| DNA | deoxyribonucleic acid |
| EFV | efavirenz, Sustiva® |
| EIA | enzyme-linked immunosorbent assay |
| FDA | (US) Food and Drug Administration |
| FTC | Emtricitabine |
| g | gram(s) |
| GCP | Good Clinical Practice guidelines |
| HAART | highly active antiretroviral therapy |
| HBV | hepatitis B virus |
| HBsAg | hepatitis B surface antigen |
| HDPE | high‑density polyethylene |
| HIV | human immunodeficiency virus |

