## Dual-energy X-ray Absorptiometry (DEXA) Scans

During the screening process, SFDPH participants will be scheduled for a whole body DEXA scan prior to enrollment. All participants who receive a Z-score of less than or equal to 2.0 standard deviations [SD] below the age appropriate mean on the baseline DEXA scan at the total spine, total hip, or femoral neck will have an evaluation of secondary causes performed as part of the study protocol. This work-up will include a thyroid stimulating hormone, 25-hydroxy vitamin D level, testosterone level, a spot urine calcium/creatinine ratio, and additional testing for other secondary causes suggested by the history and physical. Participants with a spot urine calcium/creatinine ratio of > 0.3 will have a 24-hour urine calcium level performed. In addition, participants over the age of 40 will have a serum parathyroid level checked. Participants with an abnormal work-up or with a Z-score of less than -2.5 will be referred to a primary care provider for further work-up and treatment. All participants with a Z-score of less than -2.5 SD at any of the three sites listed above, or participants who are undergoing treatment for secondary causes of low bone density, will not be eligible for enrollment.

Participants will receive subsequent DEXA scans at 12 and 24 months in the immediate arm, at 9 and 24 months in the delayed arm, and at the time of study discontinuation, if at least 6 months has passed since the previous scan. The 9 month DEXA scan in the delayed arm will be performed before the 9 month visit and before initiating study drug if possible. All other follow-up DEXA scans will be performed +/- 1 month of the target visit if possible. If a subsequent DEXA scan detects a > 5% decrease in bone mineral density from baseline at the either the total hip or total spine sites, a work-up for secondary causes (as described above) will be initiated, study product will be discontinued, and participants will continue to be followed at regularly scheduled visits until completion of study visits.

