# ADVERSE EVENTS

## Adverse Events

An adverse event (AE) is any untoward medical occurrence in a patient or clinical investigation participant administered a pharmaceutical product, regardless of causality assessment. An AE can therefore be any unfavorable and unintended sign, symptom, or disease temporally associated with the use of a medicinal product, whether or not considered related to the medicinal product. Pre-existing events, which increase in frequency or severity or change in nature during or as a consequence of use of a drug in human clinical trials, will also be considered as adverse events. AEs may also include pre‑ or post‑treatment complications that occur as a result of protocol-mandated procedures (e.g., invasive procedures such as biopsies).

An AE does not include:

- Medical or surgical procedures (e.g., surgery, endoscopy, tooth extraction, transfusion); the condition that leads to the procedure is an adverse event.
- Preexisting diseases or conditions present or detected prior to start of study product administration that do not worsen.
- Situations where an untoward medical occurrence has not occurred (e.g., hospitalization for elective surgery, social and/or convenience admissions).
- Overdose of either study drug or concomitant medication without any signs or symptoms unless the participant is hospitalized for observation.

Any medical condition or clinically significant laboratory abnormality with an onset date before the first **screening visit** is considered to be preexisting, and should be documented in the appropriate CRF. Any new event, exacerbation of a preexisting condition, or new chronic condition with an onset date after the initial screening visit but before the enrollment visit date should be documented as an intercurrent illness or new chronic condition on the appropriate CRF.

Any AE (i.e., a new event or an exacerbation of a preexisting condition) with an onset date after the enrollment visit date up to the last day on study (including any time off study medication and follow‑up), should be recorded as an AE on the appropriate CRF. If any AE occurs on study, the participant will be referred for appropriate treatment and medical supervision. All AEs judged to be clinically significant and possibly or probably related to study product, including clinically significant laboratory abnormalities, will be followed until they are no longer clinically significant or have reached a steady state.

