# STATISTICAL CONSIDERATIONS

## Study Design and Analysis Plan Overview

This is a phase II randomized double-blinded placebo-controlled trial to assess the clinical and behavioral safety of daily oral use of TDF among MSM. Four hundred MSM at risk of HIV-1 infection will be recruited from two sites, randomized 1:1:1:1 to one of four treatment arms, and followed for 24 months. Two treatment arms will receive study product (TDF or placebo) for the entire 24 months (the immediate treatment arms) and the other two treatment arms will receive no study product for the initial 9 months and then receive either TDF or placebo for the remaining 15 months. The data analysis will compare clinical and behavioral safety data between the study arms. The analysis will employ the intent-to-treat principle whereby all data from enrolled participants will be analyzed according to the initial randomization assignment regardless of how many doses they received.

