## Methods of Analysis

Analysis Populations

Intent‑to‑Treat (ITT) Population

This population will include all participants who are randomized into the study and receive at least one dose of study medication. The exclusion of participants who do not receive study drug is justified by the fact that the decision to not initiate study medication is made with no knowledge of the randomized treatment. Participants with major eligibility violations that are identifiable based on pre-randomization characteristics will be excluded. Participants who receive study medication other than that intended will be analyzed according to the group to which they were randomized.

Analysis of the Conduct of the Study

This population will include all screened participants. Specifically, summaries of the following endpoints will be generated: participant screening, eligibility, participant enrollment, participant disposition and reasons for discontinuation, participant medication compliance, participant compliance with study visits, and protocol violations/deviations. Simple descriptive statistics, including percentages, means, and quartiles will be used to summarize the distribution of these endpoints. In addition, the above analyses will be carried out by clinical site to identify any potential site-specific issues. Participants’ disposition will be tabulated as screened but never enrolled, enrolled but never initiated study product, on-study and continuing with study product, discontinued from study product but continuing follow-up for HIV infection or off-study and not continuing follow-up.

*Types of Outcomes and Statistical Analyses*

The outcomes of interest and their respective analyses can be classified by the following factors:

Type of outcome and number of responses per individual:

A) Time until first occurrence of some specified event –

One response per individual – Cox survival regression

B) Yes/no outcome;

One response – Logistic regression

Multiple responses – Longitudinal binary regression

C) Continuous outcome

In general, counts (e.g. number of partners) will be treated as Poisson distributed

outcomes while laboratory values or transformations of those values (e.g. creatinine level,

log (creatinine level) will be treated as normally distributed outcomes.

One response – Poisson, linear regression

Multiple responses – Longitudinal Poisson, linear regression

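### Clinical and laboratory safety is compared only by intent-to-treat with no end at product stop, so off-product time and recovery values count as TDF and bias mainly the laboratory and bone comparisons toward no difference

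*Protocol*

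**What the plan says.** **Analysis rule.** Section 10.1: "all data from enrolled participants will be analyzed according to the initial randomization assignment regardless of how many doses they received". The Synopsis (Statistical Methods) agrees: "Intent-to-treat analysis will be used". Section 10.4 defines one population for outcome comparisons: "This population will include all participants who are randomized into the study and receive at least one dose of study medication". It adds: "Participants who receive study medication other than that intended will be analyzed according to the group to which they were randomized".

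**Counting window.** The Synopsis limits the primary safety endpoint to "clinical adverse events and laboratory toxicities occurring after treatment initiation", which sets a start but no end. Section 9.1 records adverse events "up to the last day on study (including any time off study medication" and follow-up included.

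**Stopping and follow-up.** When a follow-up DEXA scan shows a loss above 5%, section 6.5 says: "study product will be discontinued, and participants will continue to be followed at regularly scheduled visits until completion of study visits". Section 9.6 stops product permanently for a recurrent confirmed grade 1 creatinine elevation. Product is also stopped, in some cases temporarily, for excluded medication (5.4, 6.6), post-exposure prophylaxis (6.6.1) and participant request (6.11). Sections 6.8 and 6.10 keep these men on the visit schedule to month 24.

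**Where time on product is used.** Section 10.6 (a subsequent behavioral analysis) and section 10.7 (adherence) restrict comparisons to time on product. Section 10.5 adjusts clinical safety for site and for immediate or delayed group. It has no on-product comparison and no exposure term.

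**The concern.** In a safety trial, analysis by assignment regardless of exposure is not the cautious choice, because time off drug moves the TDF arm toward placebo. The protocol itself expects this. Section 12 anticipates that most side effects will resolve quickly once product is stopped, and section 9.6 monitors men stopped for creatinine until the level returns to baseline or stabilizes. Section 10.4 plans longitudinal regression of laboratory values and names creatinine. Values measured during recovery therefore enter the TDF mean, and they come disproportionately from the men in whom the drug did something. A finding of no difference would then be hard to read: it could mean that TDF is safe, or that affected men were off it when measured.

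**Working it through.** **1. The protocol's own power (section 10.3).** Inputs: placebo SAE rate 1%, 200 men per group, type 1 error 0.05. A two-sided Fisher exact test, with power summed over both binomial distributions, gives:

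| TDF rate | Stated | Recomputed |
|---|---|---|
| 3% | 17% | 16.9% |
| 4% | 36% | 36.0% |
| 5% | 56% | 56.3% |
| 6% | 73% | 73.5% |
| 7% | 85% | 85.5% |

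The table reproduces. It applies the full TDF rate to all 200 men, with no allowance for off-product time.

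**2. Dilution of an event rate.** Let f be the share of TDF-arm time spent off product before any counted event, at placebo risk. Observed rate = p1(1 - f) + p0·f. The protocol gives no f; 10% and 20% are assumptions.

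- f = 10%: 5% × 0.9 + 1% × 0.1 = 4.6%
- f = 20%: 5% × 0.8 + 1% × 0.2 = 4.2%

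**3. What an on-product analysis would and would not recover.** Same Fisher test, true 5% v 1%:

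| Analysis | f = 10% | f = 20% |
|---|---|---|
| ITT | 4.6% v 1%: 48% | 4.2% v 1%: 40% |
| Both arms cut at stopping | 4.5% v 0.9%: 50% | 4.0% v 0.8%: 43% |
| Only TDF time shortened | 4.5% v 1%: 46% | 4.0% v 1%: 36% |

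Against 56% at full exposure, ITT loses about 8 and 16 points. Cutting both arms at stopping returns about 2 and 3 of them. If only TDF time is shortened, power falls below ITT. The loss therefore comes mainly from less drug being taken. What the on-product analysis corrects is the estimate. With person-time denominators the ratio is (4.5%/0.9) / (0.9%/0.9) = 5, against 4.6 or 4.2 under ITT.

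**4. Which stops dilute what.**

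- *Stop caused by a grade 3/4 event:* the man already counts in the primary proportion, so there is no dilution there.
- *Recurrent grade 1 creatinine:* below grade 3/4 (Synopsis) and below moderate (section 10.2.1), so it precedes any counted event.
- *Bone loss above 5%:* section 9.6 leaves it out of toxicity grading, so it also precedes any counted event.
- *Excluded medication, post-exposure prophylaxis, request:* off-product time unrelated to a counted event.
- *Longitudinal laboratory and bone values:* diluted whatever the reason for stopping.

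**5. Bone.** Scans are done at SFDPH only (section 6.5). In the immediate arms they fall at months 12 and 24, so only the month-12 scan can trigger a scheduled bone stop before month 24. In the delayed arms the month-9 scan is taken before product if possible and no later than 14 days after starting, so no scheduled on-product scan precedes month 24. The nearest figure is study 903 at 48 weeks: 6% on TDF v 2% on stavudine met that study's definition of a decrease (Introduction, Safety).

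**6. Which time counts.** Taken literally, section 10.1 includes the delayed arms' nine months without product. Planned product time in the two TDF arms would then be (100 × 24 + 100 × 15) / (200 × 24) = 3,900/4,800 = 81% of follow-up. The Synopsis starts the count at treatment initiation, which excludes those months. Section 10.1 also takes all enrolled men, whereas section 10.4 requires at least one dose and removes major eligibility violations.

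**The case against.** Intent-to-treat is a valid randomized comparison, and a supplementary on-product table is ordinary content for a statistical analysis plan, which is not at hand. The first part stands, and intent-to-treat should remain. The second does not dispose of the point: the protocol is not silent but positively sets the dose-independent rule, and it limits other analyses to time on product while leaving clinical safety out.

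The routes that stop product before a counted event may also be rare. In study 903, grade 1 creatinine elevation occurred in 3% on TDF v 2% over 96 weeks, and only 3 patients discontinued for laboratory toxicities in the first 48 weeks. This stands as a reason to expect modest dilution of event rates. It does not cover stops for non-toxicity reasons.

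Section 10.5 tabulates events by relationship to treatment and lists those leading to discontinuation. That helps a little, but it is not an on-product comparison.

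A reader might infer three stronger things that the documents do not support:

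- *That toxicity stops hide grade 3/4 events.* Such a man is already counted.
- *That an on-product analysis would restore the lost power.* It returns only about 2 to 3 points.
- *That a third or more of scanned TDF men would be off drug at month 24.* This would come from reading study 903's mean bone losses with their plus-minus values as normal SDs. The protocol neither dates those means nor labels the spread, and its reported proportions are far lower. Even the 13% at 96 weeks is too late for a stop at month 12.

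**Conclusion.** The point holds in limited form. Section 10.5 has no on-product comparison of clinical and laboratory safety, and sections 10.1 and 10.4 credit all time and values after stopping to the randomized arm. The direction, toward no difference, is clear for longitudinal laboratory and bone comparisons if effects recede after stopping, as section 12 expects. It is weaker for event rates and absent where the stop follows a counted grade 3/4 event.

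The size cannot be derived. The 10-20% loss to follow-up in section 10.3 is not a product-discontinuation rate. The shift from 5% to 4.6-4.2% rests on an assumed 10-20% of TDF time off product at placebo risk. For bone, 6% v 2% is only an anchor, for the immediate arms at one site: study 903 treated HIV-infected patients on combination therapy against stavudine, and the protocol does not give its definition of a decrease.

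This is an inexpensive improvement to the interpretation of a safety result. It does not show that the intent-to-treat comparison is invalid.

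**What to change.** 1. Keep intent-to-treat. Add to section 10.5 a pre-specified on-product TDF v placebo analysis of events and laboratory values, by product received, from first dose to last dose plus a stated window, with person-time denominators. State how temporary interruptions are handled. Thirty days is one possible window, but it needs its own justification: section 9.4 uses 30 days for reporting deaths and following ongoing SAEs, not for analysis.
2. For bone, show the last on-product DEXA scan beside the month-24 intent-to-treat result.
3. Reconcile section 10.1 (all data, all enrolled men) with the Synopsis (after treatment initiation) and section 10.4 (at least one dose, eligibility violations removed), so that one statement says which men and which time count.
4. Label the on-product result as supportive. Ending follow-up at product stop can be informative, so it does not replace intent-to-treat, and a safety conclusion need not require the two to agree.

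The cost is wording and extra tables. Dispensing records and returned tablets (5.3.1, 8.7), MEMS data (8.7) and reasons for stopping (6.11) are already collected. No visit, procedure or clinical rule changes.

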## Endpoints

### Primary Endpoints

- The clinical safety and toxicity of TDF will be assessed by the occurrence of moderate and severe clinical and laboratory adverse events in each treatment group. Mild event rates will also be reported.
- The behavioral safety will be assessed by evaluating the change in the reported type and frequency of sexual risk behaviors (e.g. unprotected anal sex, number of sex partners) in each treatment group.

### Secondary Endpoints

Secondary endpoints will include:

- assessment of adherence
- incidence of HIV infection
- incidence of antiretroviral drug resistance among those individuals who become HIV-infected over the course of the study

## Sample Size and Power Calculations

Recruitment will target 400 healthy, HIV-uninfected MSM that will be equally distributed across four treatment arms. Based on previous HIV prevention studies of similar length among MSM, it is estimated there will be an approximately 10-20% loss to follow-up over the study period.

Within the constraint of four study arms (TDF vs. placebo by immediate vs. delayed) and a total

study size of 400 participants, two design issues were explored: allocation of participants to the

four study arms and amount of time needed before the delayed arms began receipt of study

product. These evaluations were focused on the need to achieve a balance between good statistical properties (i.e., power) for the evaluation of both clinical AEs and behavioral outcomes as well as satisfy other criteria such as maximizing participation, especially in the delayed arms.

Equal allocation of participants to each study arm was found to be the best overall allocation scheme given the goals of the study. Additionally, a nine-month lead-in period for the delayed arm provided the best compromise between concerns for statistical power for comparisons of behavioral outcomes and logistical problems related to recruitment.

Sample size calculations for safety are expressed in the terms of the ability to detect SAEs. The following tables show the probabilities of observing, 0, 1, 2, 5+,  8+ or 10 or more SAEs among groups of n=100 (the immediate arm) and n=200 (both arms) for a range of possible true event rates. For example, if the true SAE rate is 3%, the probability of observing five or more events is 18.2% with n=100 and 71.9% with n=200.

**Event Probabilities for n=100**

| Event Rate  (SAE) | Probability of | | | | | |
| --- | --- | --- | --- | --- | --- | --- |
| 0 events | 1 event | 2 events | 5+ events | 8+ events | 10+ events |
| 1% | 0.366 | 0.370 | 0.185 | 0.003 | 0 | 0 |
| 2% | 0.133 | 0.271 | 0.273 | 0.051 | 0 | 0 |
| 3% | 0.048 | 0.147 | 0.225 | 0.182 | 0.010 | 0 |
| 4% | 0.017 | 0.070 | 0.145 | 0.371 | 0.048 | 0.007 |
| 5% | 0.006 | 0.031 | 0.081 | 0.564 | 0.128 | 0.128 |
| 10% | 0 | 0 | 0.002 | 0.976 | 0.794 | 0.549 |
| 15% | 0 | 0 | 0 | 1.000 | 0.999 | 0.988 |

**Event Probabilities for n=200**

| Event Rate  (SAE) | Probability of | | | | | |
| --- | --- | --- | --- | --- | --- | --- |
| 0 events | 1 event | 2 events | 5+ events | 8+ events | 10+ events |
| 1% | 0.134 | 0.271 | 0.272 | 0.052 | 0.001 | 0 |
| 2% | 0.018 | 0.072 | 0.146 | 0.371 | 0.049 | 0.049 |
| 3% | 0.002 | 0.014 | 0.043 | 0.719 | 0.254 | 0.081 |
| 4% | 0 | 0.002 | 0.010 | 0.905 | 0.550 | 0.281 |
| 5% | 0 | 0 | 0.002 | 0.974 | 0.787 | 0.545 |
| 10% | 0 | 0 | 0 | 1.000 | 0.999 | 0.996 |
| 15% | 0 | 0 | 0 | 1.000 | 1.000 | 1.000 |

The Blyth-Still-Casella 95% confidence intervals based on observing 0, 1, 2, 5, 10 events in each group are given in the following table.

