**Two-sided 95% Confidence Intervals for Various SAE Rates**

| Sample Size | 0 events | 1 event | 2 events | 5 events | 10 events |
| --- | --- | --- | --- | --- | --- |
| N=100 | (0, 3.5%) | (0, 4.9%) | (0.4%, 6.6%) | (2%, 11%) | (4.9%, 17.1%) |
| N=200 | (0, 1.7%) | (0, 2.5%) | (0.2%, 3.5%) | (1%, 5.4%) | (2.6%, 8.7%) |

Power is calculated based on the exact test (or likelihood ratio test).  The type 1 error is assumed to be 0.05.  The following table shows the power to detect the difference with various SAE rates in the treatment group given SAE rate in placebo group equals 0.01.

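### Four cells of the SAE detection tables in section 10.3 are too high, and the power table assumes full retention and gives no time window for the SAE rate

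*Protocol*

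**What the plan says.** Section 10.3 expresses sample size for safety as the ability to detect SAEs. It gives probabilities of 0, 1, 2, 5+, 8+ and 10+ events "among groups of n=100 (the immediate arm) and n=200 (both arms) for a range of possible true event rates". Its worked example, at a true rate of 3%, is that "the probability of observing five or more events is 18.2% with n=100 and 71.9% with n=200".

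Three rows matter here:

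- n=200: "2% | 0.018 | 0.072 | 0.146 | 0.371 | 0.049 | 0.049"
- n=100: "5% | 0.006 | 0.031 | 0.081 | 0.564 | 0.128 | 0.128"
- n=100: "15% | 0 | 0 | 0 | 1.000 | 0.999 | 0.988"

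On retention, the same section says "it is estimated there will be an approximately 10-20% loss to follow-up over the study period".

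On method it says "Power is calculated based on the exact test (or likelihood ratio test"), with a type 1 error of 0.05 and no mention of one or two sides. The placebo SAE rate is 0.01. Power at treatment-group rates of 3, 4, 5, 6 and 7% is given as 17, 36, 56, 73 and 85% with n=200.

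Section 3 gives the immediate arms 24 months on product and the delayed arms 15. Section 10.3 does not say over what period the SAE rate is counted.

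**The concern.** In two rows the last two columns are equal, which would mean that exactly eight or nine events cannot happen. The tables also disagree with each other. A rate of 4% in 100 men and a rate of 2% in 200 men both give an expected count of 4. The printed rows agree closely up to 8+ (0.048 and 0.049) and then part at 10+ (0.007 and 0.049).

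The power table raises two further questions: whether the stated loss was allowed for, and whether one rate can be applied to 200 men of whom half have 24 months on product and half have 15.

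These figures tell a reader, an ethics board or the safety review team what the trial can detect. Each wrong cell, and the omission of loss, errs towards more detection than the design gives.

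**Working it through.** **1. Detection tables.** Inputs are n = 100 or 200 and the tabulated rates p. The formula is P(X ≥ r) = Σ (k = r to n) C(n,k) p^k (1−p)^(n−k).

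The plan's own example comes first: P(X ≥ 5) at 3% is 0.1821 for n=100 and 0.7190 for n=200, matching 18.2% and 71.9%. Across all 84 cells, 80 agree to about 0.001 (rounding or truncation). The other four:

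| n | Rate | Column | Stated | Exact | Exact value one column left |
|---|---|---|---|---|---|
| 200 | 2% | 10+ | 0.049 | 0.0075 | 0.0493 (8+) |
| 100 | 5% | 10+ | 0.128 | 0.0282 | 0.1280 (8+) |
| 100 | 15% | 8+ | 0.999 | 0.9878 | 0.9996 (5+) |
| 100 | 15% | 10+ | 0.988 | 0.9449 | 0.9878 (8+) |

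A Poisson approximation does not explain them (0.0081, 0.0318, 0.982 and 0.930).

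**2. Power table as printed.** Inputs are 200 per group (1:1:1:1 allocation, pooled), placebo rate 1% and alpha 0.05. Power is the sum, over all pairs of counts, of the product of the two binomial probabilities wherever the two-sided Fisher p-value is at most 0.05.

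| Treatment rate | 3% | 4% | 5% | 6% | 7% |
|---|---|---|---|---|---|
| Stated | 17 | 36 | 56 | 73 | 85 |
| Fisher, two-sided, 200 per group | 16.9 | 36.0 | 56.3 | 73.5 | 85.5 |
| Fisher, one-sided, 200 per group | 26.0 | 48.2 | 68.5 | 83.1 | 91.8 |

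The two-sided test with everyone retained reproduces the table, so it contains no allowance for loss.

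**3. Loss to follow-up.** As a worst case, lost men contribute nothing: 200 × 0.90 = 180 or 200 × 0.80 = 160 per group.

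| Treatment rate | 3% | 4% | 5% | 6% | 7% |
|---|---|---|---|---|---|
| 10% loss (180 per group) | 14 | 31 | 50 | 67 | 80 |
| 20% loss (160 per group) | 11 | 26 | 43 | 60 | 74 |

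As a milder case, assume lost men contribute half their follow-up at constant hazard. The group risk is (1−L)p + L[1 − (1−p)^0.5]. At p = 7% and 1% this is 6.66% versus 0.95% for L = 10%, and 6.31% versus 0.90% for L = 20%. Power with 200 per group is then 83% and 81%.

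**4. Exposure, under an assumption.** Suppose the rate is a 24-month risk with constant hazard. The 15-month risk is 1 − (1−p)^(15/24): 1.89% for p = 3%, 4.43% for p = 7% and 0.63% for p = 1%. With half of each group at each exposure:

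- P(5+) at 3%, n=200: 0.541 instead of 0.719.
- Power for 1% versus 7% (average risks 0.81% and 5.72%): 75%, or 69% and 62% with 10% and 20% complete loss added.

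If instead the rate is the risk over the first 15 months on product, all 200 men have the same window and the correction is zero.

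**The case against.** The strongest reply is that little depends on these errors. The wrong cells are copying slips. They do not feed the worked example, the confidence intervals or the power table, and one is off by only 0.011. The 6.5-fold ratio (0.049 against 0.0075) concerns an improbable event. Section 10.3 also treats 400 as a fixed constraint, so the tables describe what that number can do. All of this stands, and it limits the consequence.

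On loss, 80% and 74% are a worst case. Section 9.1 records events to the last day on study, so a man lost midway still contributes. This also stands, with one limit: section 10.4 leaves out men who never take a dose, so a delayed-arm man lost before month 9 adds nothing on product.

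Two stronger readings are tempting and are not supported:

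- *That pooling unequal exposure is itself an error.* Section 10.7 pools all TDF and placebo participants over the first 15 months on drug for adherence, and section 10.5 speaks of at least 15 months on product. A 15-month window is therefore a natural reading, and under it n=200 is right. The exposure effect appears only under a 24-month constant-hazard reading, which the protocol does not state.
- *That naming the likelihood ratio test is a mistake.* The asymptotic version does give other figures (36, 57, 74, 86 and 93%). An exact conditional test ordered by the likelihood ratio, with 200 per group, gives the same 16.9, 36.0, 56.3, 73.5 and 85.5% as Fisher. The wording is loose but can describe the calculation that was done.

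**Conclusion.** The point holds in two parts, with a third that is conditional.

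- **Wrong as printed:** exactly four cells, all too high. This rests on no assumption beyond the binomial model that the other 80 cells follow.
- **Stated but unused:** the 10-20% loss. The printed 85% for 1% versus 7% requires all 200 men per group. It becomes 80% and 74% if lost men contribute nothing, and about 83% and 81% if they contribute half their follow-up. The half is an assumption made here.
- **Undetermined:** the effect of the delayed arms' 15 months. It is nil with a 15-month window. With a 24-month window and constant hazard, P(5+) at 3% drops to about 54% and power at 7% to about 75%, before loss.

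A reader might want one replacement range for power at 7%. The documents do not support one, because the result depends on the window and on how much follow-up lost men give. Nor do these errors show that 400 participants is the wrong number.

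**What to change.** In section 10.3:

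1. Correct the four cells: n=200, 2%, 10+ to 0.007 (exact 0.0075); n=100, 5%, 10+ to 0.028; n=100, 15%, 8+ to 0.988 and 10+ to 0.945.
2. Label the power table as a two-sided Fisher exact test at 0.05 with 200 participants per group and full retention.
3. Add power rows at 10% and 20% loss, saying how much follow-up lost men are assumed to contribute.
4. State the period over which the SAE rate is counted. If it is the first 15 months on product, the n=200 figures need no exposure correction. If it is 24 months, recompute the n=200 detection and power tables with 100 men at 24 months and 100 at 15 months per treatment, and state the hazard assumption.

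The cost is restated figures and two or three sentences. Sample size, allocation and conduct are unchanged.
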